## Abstract

**Background:**

Need for recovery and work ability are strongly associated with high employee turnover, well-being and sickness absence. However, scientific knowledge on effective interventions to improve work ability and decrease need for recovery is scarce. Thus, the present study aims to describe the background, design and protocol of a cluster randomized controlled trial evaluating the effectiveness of an intervention to reduce need for recovery and improve work ability among industrial workers.

**Methods/Design:**

A two-year cluster randomized controlled design will be utilized, in which controls will also receive the intervention in year two. More than 400 workers from three companies in Denmark will be aimed to be cluster randomized into intervention and control groups with at least 200 workers (at least 9 work teams) in each group. An organizational resources audit and subsequent action planning workshop will be carried out to map the existing resources and act upon initiatives not functioning as intended. Workshops will be conducted to train leaders and health and safety representatives in supporting and facilitating the intervention activities. Group and individual level participatory visual mapping sessions will be carried out allowing team members to discuss current physical and psychosocial work demands and resources, and develop action plans to minimize strain and if possible, optimize the resources. At all levels, the intervention will be integrated into the existing organization of work schedules. An extensive process and effect evaluation on need for recovery and work ability will be carried out via questionnaires, observations, interviews and organizational data assessed at several time points throughout the intervention period.

**Discussion:**

This study primarily aims to develop, implement and evaluate an intervention based on the abovementioned features which may improve the work environment, available resources and health of industrial workers, and hence their need for recovery and work ability.

## Background

The public finance and social welfare of western societies is challenged by demographic changes and increasing global commercial competition. Unskilled and semi-skilled workers (blue-collar workers) have an elevated risk of premature and hence costly drop-out from the labor market compared to skilled and white collar workers [1], possibly due to high physical work demands negatively influencing their health [2].

High work demands require high efforts which may deplete the resources of the workers. Over a time period, if sufficient recovery opportunities are not present, continuous depletion of resources can lead to negative effect on individual’s health and well-being and ultimately, in absence of adequate recovery, lead to negative long-term effects such as exhaustion, losses of function, and physical and mental impairment [3,4].

Recent studies demonstrate that these long-term effects are preceded by short-term effects which are indicative of acute current fatigue such as need for recovery (*a person*’*s desire to be temporarily relieved from demands in order to restore his or her resources*) ([4], p. 330)). Need for recovery is a very early stage of long-term strain process, and is noticeable in the immediate off-work situation [4]. If sufficient recovery is not achieved, a person must exert additional effort to meet the demands of job next day, and this process may start a vicious cycle leading to prolonged fatigue [4]. Empirical studies have shown that an elevated need for recovery is a predictor of high employee turnover [5], impaired well-being [6], sickness absence [5], psychosomatic [7], sleep and emotional complaints among workers [8]. Therefore, a high need for recovery after work might be a useful indication for the need to initiate preventive interventions and aim to achieve a personal psycho-physiological homeostatic balance [9].

Another scientific concept reflecting the balance between demands and resources of workers is work ability [10,11] defined as “*how good is the worker at present*, *in the near future*, *and how able is he/she to do his/her work with respect to work demands, health, and mental resources*” ([12], p. 3). A decreasing work ability has been documented to be associated with high work demands [13-15], low work resources and stress and burnout [16,17], as well as being a predictor for future sickness absence [13,18] and early retirement [13,19].

A significant proportion of the work tasks in industrial production is performed by blue-collar workers. Blue-collar workers generally experience higher fatigue and need for recovery [8,20] and increased risk of reduced or impaired work ability [21-23]. These conditions make it challenging for blue-collar workers to remain in the workforce until the age of retirement. To the best of our knowledge, few workplace interventions studies have attempted to reduce the need for recovery among blue collar workers [24-26]. Two studies have observed positive results from interventions to reduce need for recovery and increase work ability among female healthcare workers [25,26]. However, it has not been investigated if these intervention effects can be generalized to other work sectors. Similarly, many interventions have focused on improving the work ability of workers, but most studies have observed minor or no improvements [27-30]. Although the ground principle of improving work ability and need for recovery is similar (restoring the balance between demands and resources), none of the previous studies have conducted an intervention focusing on both of these concepts among blue-collar workers [24-30].

The general recommendations for conducting workplace health intervention is that success is more likely if (a) it considers multifactorial components of workers’ health [31], (b) is non-expert driven [32], (c) utilizes a structured approach for generating new action plans and subsequent implementation [33-35], (d) utilizes a participatory approach, and (e) optimally utilizes available resources in the organization to facilitate the implementation of new interventions [31]. It is furthermore important to utilize a multi-dimensional approach, focusing on organizational, psychosocial and physical (ergonomic) work environment factors, in interventions aiming to reduce the need for recovery and improve work ability, as both work ability and need for recovery concepts build on a bio-psycho-social framework [36-38]. Previous studies have predominantly used predetermined expert-developed interventions targeting need for recovery [25] and work ability [27,39]. However, expert driven interventions often result in high noncompliance and problems matching the intervention to the expectations and needs of participants [28]. Thus, tailoring of the intervention through a participatory approach has been shown to promote sustainability of the intervention, empowerment of the workers, increased commitment to the intervention, and increased credibility and implementation of the intervention at multiple levels of the organization [35,40-42]. Another key element to consider when planning an effective intervention is the optimal utilization of available resources in the organization (e.g. health and safety initiatives, management, human resources, and specialists) [31] to facilitate the intervention. The adaptation to contextual resources ensures a better fit of the intervention with the organizational culture, reduces the need for the research group or external consultants to run the intervention and likewise empowers the employees and managers who instead run the intervention, contributes to smooth implementation of the intervention and hence minimizes the financial costs for the company [35]. Finally, interventions targeting need for recovery or work ability are mostly conducted at the individual level only [24,25,27,28,39] with no or short-lasting effects [24,28]. In contrast, organizational interventions [35,43] have the potential to reduce or remove the causes of strain for entire work groups [44] and not only for vulnerable workers. Thus, organizational level interventions are generally recommended for intervening on occupational health problems [45].

To summarize, effective interventions for reducing need for recovery and improving work ability theoretically require a bio-psycho-social, participatory, and structured organizational approach, involving all levels of the organization (i.e. individual, group, leader and organizational) and optimally using the onsite resources.

Therefore, the aim of our study is to evaluate the effectiveness of an intervention based on the aforementioned features on need for recovery and work ability among industrial workers. The objective of this paper is to present the background, design, protocol and evaluation of the “Participatory Physical and Psychosocial Intervention for Balancing the Demands and Resources among Industrial Workers” (PIPPI) intervention. The primary hypothesis of PIPPI is that the intervention will decrease the need for recovery and improve the work ability of the workers.

## Methods

The CONSORT statement is utilized to describe the design and protocol of this study [46].

### Study design

The study is a two-year cluster-randomized trial in which controls also receive the intervention in year two (Figure 1). The abovementioned primary hypothesis will be tested in the first year of intervention, while the sustainability of the intervention will be analyzed in the second year of the intervention.

**Figure 1 Fig1:**
[figure not shown]
**Design of the Participatory Physical and Psychosocial intervention for Balancing the Demands and Resources**
**(PIPPI) cluster randomized controlled study.** T0 = time at baseline, T1 = Time at first follow-up (12 months after baseline), T2 = Time at second follow-up (12 months after first follow-up).

This trial has been registered in the Danish Data Protection Agency register (Journal number: 2013-54-0329) and in the International Standard Randomized Controlled Trial Register (ISRCTN76842602, date assigned: 10 July 213)). Moreover, this study has been approved by the Ethical Committee for the regional capital in Denmark (Journal number: H-2-2013-FSP13) and will be conducted in accordance with the Helsinki declaration [47].

### Study population

This study aims to recruit larger industrial workplaces in Denmark employing workers organized in teams mainly carrying out manufacturing work.

The inclusion criteria at the *workplace level* is that the workplace should (a) have at least 100 employees mainly involved in manual labor work, (b) be team based, (c) have a fairly cooperative relation between different levels of organization, (d) be willing to implement the PIPPI activities and (e) reflect the geographical and organizational distribution of Danish industrial production companies. Inclusion criteria at the *team level* are that the employees are organized in teams of formal work groups. Inclusion criteria at the *individual level* are that the participants should (a) work for ≥20 hours/week and (b) give consent to participate in the scientific evaluation of the study. PIPPI is an organizational-level intervention and all workers in the intervention group will participate in intervention activities. Thus, there are no individual exclusion criteria for participating in the intervention activities. However, only the workers who satisfy the individual level criteria will be included in the effect evaluation of this study.

### Recruitment

Recruitment of the companies will be done by collaborating with worker and workplace/trade unions and industrial associations. Based on the previously mentioned inclusion criteria at workplace level, the unions will be asked to provide a list of potential participating companies. The research group will contact the management of the suggested companies via email and phone, and describe the content and requirements for participating in the study. If the management shows interest in participating in the study, a meeting will be conducted for the management and worker representatives of the workplace and research the possibility for participation in the study. Once the collaboration is confirmed, details about the team level recruitment criteria, organization of the project, communication plan, intervention content, intervention implementation at all levels and establishment of local project steering group consisting of management and worker representatives, human resources employees and researchers, and their responsibilities will be explained and settled.

An information meeting will be arranged for workers where the signed consent form will be obtained from workers who wish to participate in the study. Workers will also receive information about the intervention via information meeting videos uploaded at the workplace’s homepage, via distribution of information leaflets and via posters displayed on accessible locations. The interested workers will sign informed consent forms which will be collected with the support from team leaders and key contact person at the workplace.

### Randomization

The working teams will be randomized to either the intervention group or control group utilizing cluster level randomization. A randomized block design will be utilized to prevent contamination between participating adjoining team. Thus, the working teams will be structured in blocks based on their geographical proximity and common leaders. These blocks will then be randomized into either control or intervention groups using a computer generated randomization schedule. In the second phase of the intervention, the control group will also receive the intervention.

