### Statistics

The effect of the intervention on the primary and secondary outcomes will be performed using a multi-level mixed model or generalized linear mixed models (GLMM) based on comparison between the intervention and the control group from baseline (T0) to 12 months after baseline (T1). Four levels will be included in the mixed model: time (measurement time points), worker, working team and enterprise. The multi-level analyses will concurrently take into account the clustering of observations of workers within the working team, as well as repeated measurements within each worker. Sensitivity analyses will be conducted under different assumptions about missing data [68].

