### Sample size calculation

The sample size was calculated based on the standardized effect size, a standardized difference between intervention and control groups. On the one hand, the PIPPI intervention is extensive, targeting a range of challenges in the work environment at various levels of the organization. On the other hand, the intervention is not equally intensive for every employee – the intensity depends on a number of circumstances, e.g. the number of action plans designed and completed in the work group, or whether the employee participates in the individual visual mapping session with his or her line manager. Thus on average, we assumed a medium effect size, corresponding to a standardized difference score of 0.50 [69].

Because we are not aware of any previous similar intervention study among manufacturing workers, we assume an intra-class correlation of .05 based on a previous cluster randomized controlled study on prevention of low back pain and its consequences among nurses’s aides in elderly care in Denmark [70]. With level of significance (α) of .05, a statistical power (1-β) of 0.9, intra-class correlation of .05, and a design effect of 1.54 (considering average cluster size of 22 workers), 200 (9 teams) workers in each group will be required.

Generally, workplace intervention studies have a high dropout rate. Also, there is a risk of organizational changes happening at workplace which can lead to drop-out of entire cluster from the evaluation. Therefore, we are aiming to randomize more than 400 workers (more than 18 teams) in both groups.

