### Limitations and risks

The first limitation of this intervention is that the action plans generated through the workshops and participatory approach may differentially target combinations of work demands and resources among the working teams. However, this aspect of the PIPPI intervention also acts as a strength of the study as this tailors the intervention activities to the specific needs, resources, wishes and barriers of the participating workers. The heterogeneity of the intervention content and implementation may therefore be necessary in order to obtain positive effects. Finally, the limitation of a participatory approach is that some action plans may focus on areas that are perceived by employees as highly relevant, but are unrelated to need for recovery and work ability. Though this is unlikely for the majority of action plans, we collect information on all actions developed to monitor the content and targets of the activities.

Another limitation is that the control group may start activities to improve work ability and need for recovery themselves or even seek some of the intervention activities on their own or inadvertently receive some aspects of the intervention (e.g. because of intervention activities initiated from a higher organizational level). This limitation will be addressed by using a cluster-randomization which will reduce the contamination between the groups by ensuring that the groups are not sharing the same geographical area and managers. Additionally, the steering group will also be informed about this issue to ensure that the actions developed by the intervention group are not implemented among the controls in the first follow-up period.

A potential risk factor for this trial is the senior management’s interest and motivation in the project which may diminish if the intervention fails to make progress according to their expectations. The role of senior management is vital for successfully planning, implementing and evaluating the intervention [75]. To address this risk, we will utilize different strategies to ensure managers readiness for change and motivation, such as involving them in the steering committee, and ensuring support for the intervention from them by discussing the intervention content with them.

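### Blocks of teams are allocated to the arms, but the sample size and the mixed model take the single team as the cluster and leave the block out

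*Protocol article*

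**What the plan says.** The Randomization section of the protocol article gives two accounts of the unit. It opens with "The working teams will be randomized to either the intervention group or control group utilizing cluster level randomization". It then explains that, to limit contamination between adjoining teams, "the working teams will be structured in blocks based on their geographical proximity and common leaders", and concludes: "These blocks will then be randomized into either control or intervention groups using a computer generated randomization schedule". The Limitations and risks section fits the second account, since it relies on "ensuring that the groups are not sharing the same geographical area and managers".

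The Statistics section lists the levels of the analysis: "Four levels will be included in the mixed model: time (measurement time points), worker, working team and enterprise". It describes clustering as workers within the working team. The Sample size calculation section takes the same unit: "a design effect of 1.54 (considering average cluster size of 22 workers), 200 (9 teams) workers in each group will be required". The block appears in neither section. The number of blocks, the number of teams in a block and any correlation between teams of one block are not stated.

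**The concern.** These are not stratifying blocks within which both arms are represented. The block itself receives the arm, so it is the randomised cluster, and all its teams are always in the same arm. Variation between blocks therefore goes straight into the arm contrast. A model that stops at the team treats those teams as independent.

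Correlation within a block is plausible on the article's own account. Teams in a block share a leader and an area. Line managers are trained as ambassadors, hold the individual talks and mapping sessions, and are responsible for daily implementation; the article names their failure to fulfil this role as a risk to the trial. Teams under one leader thus share a driver of change in both primary outcomes. At stake are the width of the confidence interval, the 5% error rate and the stated power.

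**Working it through.** **Inputs from the Sample size calculation section.** Effect: "we assumed a medium effect size, corresponding to a standardized difference score of 0.50". "With level of significance (α) of .05"; sidedness is not stated, and two-sided is assumed. Power 0.90, ICC 0.05, average cluster m = 22, 9 teams per arm (9 × 22 = 198 workers; the article says 200).

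**Reproducing the plan's figure.**
- Without clustering, d = 0.5 needs 85 workers per arm.
- Design effect from the stated inputs: DE = 1 + (m − 1) × ICC = 1 + 21 × 0.05 = 2.05.
- 85 × 2.05 = 174.25 workers; 174.25 / 22 = 7.92, so 8 teams. One extra cluster per arm for small numbers gives 9 teams, or 198 workers, which is close to 200.
- Noncentral t on 2 × (9 − 1) = 16 df: power is 0.903 with 9 teams and 0.861 with 8. There is almost no slack.
- The printed design effect of 1.54 gives 85 × 1.54 = 131 workers and does not lead to 200. It conflicts with m = 22 and ICC 0.05. That is a separate error, and everything below starts from 2.05.

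**Adding the block (assumptions).** Let k be the teams per block (2 or 3) and rb the correlation between workers in different teams of one block. Keep the within-team ICC at 0.05 and let 0%, 25%, 50% or 100% of it lie at block level (rb = 0, 0.0125, 0.025, 0.05). For a single post-intervention outcome:

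DE = 1 + 21 × 0.05 + (k − 1) × 22 × rb; effective n = 198 / DE; noncentrality = 0.5 × √(effective n / 2); df = 2 × (9/k − 1), which is 7 for k = 2 and 4 for k = 3.

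| k | rb | DE | Power, t on block df | Power, normal approx. | True SE / team-level SE = √(DE/2.05) |
|---|---|---|---|---|---|
| 2 | 0 | 2.05 | 0.845 | 0.935 | 1.00 |
| 2 | 0.0125 | 2.325 | 0.798 | 0.904 | 1.07 |
| 2 | 0.025 | 2.60 | 0.754 | 0.870 | 1.13 |
| 2 | 0.05 | 3.15 | 0.673 | 0.800 | 1.24 |
| 3 | 0 | 2.05 | 0.739 | 0.935 | 1.00 |
| 3 | 0.0125 | 2.60 | 0.642 | 0.870 | 1.13 |
| 3 | 0.025 | 3.15 | 0.564 | 0.800 | 1.24 |
| 3 | 0.05 | 4.25 | 0.452 | 0.675 | 1.44 |

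Using 200 workers instead of 198 changes these powers by less than 0.01.

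With k = 2 there are on average 4.5 blocks per arm. For whole numbers, and rb from 0.05 down to 0.0125, power is 0.600 to 0.728 with 4 blocks (176 workers, 6 df) and 0.735 to 0.852 with 5 blocks (220 workers, 8 df).

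**Where 0.90 would survive.** By normal approximation, 200 workers per arm keep 0.90 while DE ≤ 2.38. That means rb ≤ (2.38 − 2.05) / 22 = 0.015 for k = 2, and rb ≤ (2.38 − 2.05) / 44 = 0.0075 for k = 3.

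**The case against.** The strongest reply is that the consequences are not established. A reader might infer that 0.90 power is certainly missed and that the standard errors are certainly too small. The article does not support that: it gives neither block size nor block correlation. At rb = 0 a team-level standard error is correct, and by normal approximation two-team blocks with rb = 0.0125 still reach 0.90. Part of the loss in the t column comes from the few degrees of freedom alone (0.845 at rb = 0 with two teams). The lowest value, 0.45, assumes that the whole ICC lies at block level, although workshops and action plans are run team by team. This stands, and it makes the point conditional.

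A reader might also turn the standard error ratios into an error rate for this trial. That does not follow. The planned comparison runs from baseline to 12 months, so stable differences between leaders or areas largely cancel and only block-by-time variation remains. The excess over 5% may be smaller than a single-outcome calculation suggests.

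Nor should the whole step from 1.54 to, say, 2.325 be put down to blocks: 0.51 of it is the misprinted design effect and 0.275 is the block.

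Two further replies carry less weight. The enterprise level may absorb some variance above the team. But both arms appear to sit within a company, because the steering group is to keep intervention actions away from controls; company differences then largely cancel, while block differences do not. The aim of more than 18 teams is an unquantified reserve for dropout. Finally, this is not detail left to an analysis plan: the article itself lists the model levels and the cluster size, and both conflict with its own allocation rule.

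**Conclusion.** The mismatch is clear. On the operative wording, supported by the Limitations section, the block is the randomised unit, and the stated model and sample size omit it. The opening sentence of the Randomization section says otherwise and has to be reconciled.

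The consequences are conditional on blocks of more than one team and on positive correlation in outcome change between teams of a block. The first is implied by forming blocks from adjoining teams with common leaders; the second is plausible but unquantified. Under the assumptions above, power is about 0.67 to 0.80 (two teams) or 0.45 to 0.64 (three teams) on block-level degrees of freedom, and 0.80 to 0.90 or 0.67 to 0.87 by normal approximation, against 0.903 with 9 independent teams per arm. These figures are illustrations for a single post-intervention outcome, not estimates for the planned model. A type I error above 5% is possible on the same conditions, and its size cannot be stated from the article.

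**What to change.** - **Randomization:** reconcile the two statements so that one unit is named as randomised.
- **Statistics:** add the randomised block as a random level, with team nested in block, and include block-by-time variation. A block intercept alone would do little for the baseline-to-12-month arm contrast. Base the test of the arm effect on block-level degrees of freedom; the particular small-sample method can be left to the analysis plan.
- **Sample size calculation:** state the planned number and size of blocks per arm and an assumed block-level correlation with a range. Restate the design effect and power with the block as the cluster, starting from 2.05 rather than 1.54.

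The cost is wider confidence intervals and a less favourable stated power. No extra data are needed for these changes. Whether the number of blocks is then adequate can be judged only once it has been stated.
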